### Analysis Plan

The CONSORT (Consolidated Standards of Reporting Trials) guidelines will be used in reporting the results. The biostatistician shall be blinded to the group allocation. The process of client selection and flow throughout the study will be summarized using a flow diagram. The analysis of client demographics and outcome variables shall be summarized using descriptive summary measures, expressed as mean (standard deviation) or median (range) for continuous variables and number (percentages) for categorical variables. All outcomes shall be analyzed using an intention-to-treat principle where data from participants shall be analyzed according to the group to which they were randomized even if they do not receive the allocated intervention. Missing data shall be handled using the multiple-imputation method. The student *t* test and analysis of variance for comparing group means will be used. All statistical tests shall be performed using two-sided tests at the 5% level of significance. The Bonferroni method shall be used to adjust the level of significance for testing of secondary outcomes to keep the overall level at an alpha of 5%. For all group comparisons, the results shall be expressed as an effect (or risk ratio for binary outcomes), corresponding two-sided 95% confidence intervals, and associated *P* values. *P* values shall be reported to three decimal places with values less than .001 reported as <.001. Adjusted analyses using baseline variables shall be performed using regression techniques to determine the continuing influence of key baseline characteristics on the outcomes. The Kaplan-Meier survival analysis will be used for timed variables like mortality. All analyses will be performed using SPSS version 25.0 (IBM Corp) for Windows. Adherence will be measured both as a continuous outcome (change in adherence) and as a binary outcome (ie, adherent, 95% of pills taken, or nonadherent, <95% of pills taken) following the composite adherence score method. Adherence data shall be handled in a number of ways, reported as the number of doses respected, and shall be combined into a composite score. The effects of the intervention shall be reported on all the measures of adherence used and will be compared for discrepancies.

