### Participants: Inclusion and Exclusion Criteria

The study population shall include HIV clients either coinfected with or without tuberculosis who come to the hospital for a routine health evaluation. Participants shall be consecutively recruited and randomly allocated to the intervention and control groups.

We shall include clients who are 21 years or older, have access to or own a mobile phone and can read text messages, and who have been on ART for at least a month and planned to live in Cameroon during the period of the study. We shall place more emphasis on clients who have started ART for at least 1 month to measure the differential effects for clients initiating ART versus those who have been under treatment for longer durations. Informed consent is a prerequisite for participating in the study and shall be provided orally and in writing.

We shall exclude clients who have been on ART for less than a month and who are younger than 21 years. Clients who have used ART for at least 1 month are chosen to enable us to be able to calculate a baseline figure for treatment adherence.

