	**Adherence at baseline and at 2, 4, and 6 months**					
		Self-report	Ordinal	Binary	% adherence in last month >95%	Risk ratio
		Pill identification test	Ordinal	Binary	% of pills identified >95%	Risk ratio
		PRD^a^	Ordinal	Binary	% of complete refills >95%	Risk ratio
		VAS^b^	Ordinal	Binary	VAS percentage >95%	Risk ratio

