**Secondary**						
	Weight		Ratio	Continuous	Change in weight	*t* test
	BMI		Ratio	Continuous	Change in BMI	*t* test
	Viral load		Ratio	Continuous	Change in viral load	*t* test
	OIs^c^ (AFB^d^ diagnosis)		Nominal	Binary	Occurrence of new OI (AFB positive smear)	Chi-square test
	Mortality		Nominal	Binary	All deaths	Chi-square test
	Satisfaction with care		Ordinal	Categorical	Change in satisfaction scores	*t* test
	QoL^e^		Ordinal	Categorical	Change in QoL scores	*t* test

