### Sample Size Determination

The sample size determination is based on the test of the null hypothesis that the rates of adherence to ART in the intervention and control groups are equal. The primary measure of effect is the rate of adherence to ART as measured by using the VAS over 6 months. Given the information from previous studies [10,11], it is estimated that approximately 60% of participants would maintain adherence ≥95% without intervention and that the interventions would help 82% of the participants maintain ≥95% adherence. A two-sided test is assumed where an effect in either direction will be interpreted at a significance level of 5%. The study will have a power of 80% to yield a statistically significant result using a chi-square test (assuming an intention-to-treat principle for the analysis) of the relative risk at an alpha level of 5% to detect a 25% difference (60% vs 85%).

The formula for calculating the sample size for randomized controlled trials by Chan [26] is used.

where c=7.9 for 80% power and p1 and p2 are the proportion estimates (60% for the control group and 85% for the intervention group).

[figure not shown]

It is assumed that 10% of the participants shall drop out of the study due to loss to follow-up and mortality. A total of 52 participants shall be randomized to each arm to allow for the 10% drop out. Therefore, the required sample size will be 156 (52 x 3 = 156) participants.

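### The binary adherence effect is fixed as a risk ratio with no baseline adjustment named, and the planned regression is not designated as the SMS effect estimate, so precision is given away

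*Protocol article*

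**What the plan says.** - **Baseline adherence is wanted and collected.** Under Participants: Inclusion and Exclusion Criteria, clients need at least one month of ART and are "chosen to enable us to be able to calculate a baseline figure for treatment adherence". Table 1 lists adherence at baseline and at 2, 4 and 6 months.
- **Effect measure for adherence.** The analysis-method column of Table 1 gives a risk ratio for each of the four adherence measures, all dichotomised at 95% (for self-report, "adherence in last month >95"%).
- **Continuous secondary outcomes.** Table 1 lists change from baseline with a t test, for example "Change in weight", and likewise for BMI and quality of life. The Analysis Plan adds analysis of variance for comparing group means.
- **Role of regression.** The Analysis Plan states: "Adjusted analyses using baseline variables shall be performed using regression techniques to determine the continuing influence of key baseline characteristics on the outcomes". The abstract describes the covariate analysis in the same way, as a search for factors that influence outcomes.
- **Power.** Under Sample Size Determination the expected benefit is first put as "the interventions would help 82% of the participants maintain ≥95% adherence", against 60% without intervention. The calculation then uses 85%. It assumes a chi-square test, 80% power and 52 per arm after 10% dropout.

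**The concern.** The baseline value of an outcome is usually among its strongest predictors. Here it is available for adherence, and eligibility was shaped to obtain it, but the effect measure fixed for binary adherence names no adjustment for it. The one place where baseline variables enter a model describes that model as a study of prognostic factors, so on the wording given the reported SMS effect would be the unadjusted risk ratio.

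Bias is not at issue, because randomization protects the unadjusted comparison. What is at stake is precision, and robustness to chance imbalance in small arms. Recruitment is complete at 160, so the analysis is the only place left to gain information. A t test on change does use the baseline value, but gives it a fixed weight of one, which is inefficient unless the correlation with follow-up is high.

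**Working it through.** **1. The plan's own sample size.** Inputs from Sample Size Determination: c = 7.9, p1 = 0.60, p2 = 0.85, dropout 10%.

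n = c[p1(1−p1) + p2(1−p2)]/(p2−p1)² = 7.9 × (0.2400 + 0.1275)/0.0625 = 46.45 evaluable; 46.45/0.9 = 51.6, so 52 per arm. The stated figure is reproduced. Evaluable per arm: 52 × 0.9 = 46.8, about 47.

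**2. Power of the planned unadjusted comparison** (one SMS arm vs control, pooled chi-square, two-sided 5%):

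| Rates | 47 per arm | 52 per arm |
|---|---|---|
| 60% vs 85% | 78.4% | 82.4% |
| 60% vs 82% | 65.6% | 70.1% |

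**3. Chance imbalance at baseline.** Baseline adherence of 60% is assumed, borrowing the control rate. The standard error of the difference between two arms of 52 is √(2 × 0.6 × 0.4/52) = 0.096. A gap of 10 points or more in either direction is 0.10/0.096 = 1.04 standard errors, which happens in about 30% of trials.

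**4. Gain for binary adherence.** The documents give no baseline-to-follow-up correlation, so a range is shown. Simulation: 6,000 trials per setting, 47 per arm, baseline adherence 60%, baseline and follow-up generated from correlated normal variables cut at the required rates, linear probability model with robust standard errors, with and without binary baseline adherence as covariate. Monte Carlo error near 68% is √(0.68 × 0.32/6000), about 0.6 points.

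| Latent correlation (assumed) | 60% vs 82% | 60% vs 85% |
|---|---|---|
| Unadjusted | about 68% | about 81% |
| 0.3 | 69% | 81% |
| 0.5 | 71% | 83% |
| 0.7 | 77% | 88% |
| 0.8 | 81% | 91% |

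The unadjusted figures are 2 to 3 points above step 2 because the robust test does not pool the variance. The comparison that matters is within each column.

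A simpler approximation, effective n = n/(1−ρ²) with ρ the correlation between the observed binary values, gives more: at ρ = 0.5, 47/0.75 = 62.7 and power of 78.1% at 60% vs 82%. Dichotomising weakens a latent correlation, so the two scales are not interchangeable. The latent-scale figures are the cautious ones and are used here.

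**5. Gain for continuous outcomes.** Let the outcome have the same variance σ² at baseline and follow-up, with correlation r.

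- Change score: variance 2(1−r)σ².
- ANCOVA: residual variance (1−r²)σ².
- Ratio: (1−r²)/[2(1−r)] = (1+r)/2, which never exceeds 1.

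| r (assumed) | Ratio | Variance reduction |
|---|---|---|
| 0.3 | 0.65 | 35% |
| 0.5 | 0.75 | 25% |
| 0.7 | 0.85 | 15% |
| 0.9 | 0.95 | 5% |
| 0.95 | 0.975 | 2.5% |

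**The case against.** The strongest reply is that adjustment is already planned. The Analysis Plan commits to regression with baseline variables, nothing says that arm is left out of those models, and a condensed article may leave the covariate list to an analysis plan that is not shown. This stands in part: it would be wrong to say that adjustment is absent. But the article does fix an analysis method for each outcome in Table 1, and it states the purpose of the regression twice, each time as identifying influential characteristics. The role of the regression is therefore a stated choice, and that choice can be improved.

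It is also fair that unadjusted risk ratios and t tests on change are valid in a randomized trial, that the gain depends on a correlation the documents do not give, and that at a latent correlation of 0.3 the gain in adherence power is only about a point.

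A reader might infer several stronger things that the text does not support:

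- *That the trial is simply underpowered.* At the design effect of 60% vs 85% the sample size reproduces. The shortfall (about 66% to 70%) appears only at the protocol's own 82%, and the conflict between 82% and 85% is a separate matter.
- *That baseline adherence is ignored.* The Analysis Plan also analyses change in adherence as a continuous outcome, and Table 1 lists change in the composite measure.
- *That three arms cannot be compared.* Analysis of variance is named alongside the t test.
- *That hospital is excluded, or that visits are tested separately.* No covariates are listed, so exclusion is not shown. Separate testing at each visit is an inference from the table layout.

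**Conclusion.** The point holds as a matter of efficiency, not validity. For binary adherence, a primary outcome, the effect measure is fixed with no baseline adjustment named, and the planned regression is not designated as the SMS effect.

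The gain in power for adherence runs from about 1 to 13 points at 60% vs 82%, and from almost nothing to about 10 points at 60% vs 85%. This rests on 47 evaluable per arm, an assumed 60% baseline adherence and assumed latent correlations of 0.3 to 0.8. It was computed for a risk difference at one time point, so it indicates the gain from a log-link model without being an exact figure for it.

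For continuous outcomes the loss is material only at moderate correlation, which may apply to quality of life. For weight and BMI it is probably 5% of the variance or less, if r is 0.9 or more. Retention has no baseline value, so the point does not reach that primary outcome.

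**What to change.** In the Analysis Plan and Table 1:

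1. Name as the main adherence estimate the risk ratio for each SMS arm versus control from a log-link model (modified Poisson with robust standard errors) that includes baseline adherence. Hospital may be added as a covariate, and a repeated-measures version over months 2, 4 and 6 is an option.
2. Replace the t test on change by ANCOVA on the follow-up value with the baseline value as covariate. This matters mainly for quality of life and other outcomes with moderate correlation; for weight and BMI little changes.
3. Keep the unadjusted risk ratios and change comparisons as supportive results, and keep the study of influential baseline characteristics as a separate, secondary use of regression.

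The cost is wording and a little programming. Baseline adherence is already collected, and no extra participants or visits are needed. The change should be recorded before anyone sees results by arm, so that the choice between adjusted and unadjusted estimates cannot depend on the data.

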### Patient and Public Involvement

This study was conceived and designed to address gaps in the care and support available to people living with HIV/AIDS who are receiving ART. The intervention was designed with the active involvement of patients with HIV, their caregivers, and health workers through focus group discussions. Our randomized controlled trial offers participants the opportunity to provide feedback regarding the burden of the intervention through focus group discussions involving a cross-section of participants.

### Ethics and Dissemination

Ethical clearance for this trial was obtained from the Institutional Review Board of the Faculty of Health Sciences of the University of Buea in Cameroon (Reference number: 2018/147/UB/SG/IRB/FHS). Administrative authorization was obtained from the Regional Delegation of the Ministry of Public Health for the South West Region and the District Health Services. The purpose of the study and the role of the participants will be well explained in the consent form to the participants and participation shall only take place after the participant has read and signed the informed consent forms voluntarily. The informed consent shall include signed permission to consult the client’s medical records over the duration of the study.

Dissemination efforts shall target individuals and institutions that will have the most impact on local, national, and international HIV and AIDS policies. Therefore, dissemination plans shall include the presentation of research findings in seminars, conferences, and scientific publications in peer-reviewed journals. A summary of the findings will be made available to participants.

## Results

Recruitment of participants in the trial took place in May and June 2018. Recruited participates were randomly allocated to the intervention and control arms at the start of the intervention in July 2018.

A total of 160 participants have been recruited and randomly allocated into the intervention and control groups. Participants were allocated into 3 groups (52 in the once weekly SMS, 55 in the twice weekly SMS, and 53 in the control). Data collection and analysis are ongoing, and statistical results will be available by the end of August 2019.

## Discussion

Since the launch of the fast track approach to end the AIDS epidemic by 2030, Cameroon is far from reaching the 90-90-90 treatment target in 2020, whereby 90% of people living with HIV know their HIV status, 90% of people who know their HIV-positive status are accessing treatment, and 90% of people on treatment have suppressed viral loads [27]. Only 58% of people living with HIV know their HIV status, 37% of those living with HIV are on treatment, and 19% of these patients are virally suppressed 2 years from the 2020 treatment target in Cameroon [27].

New strategies to end the AIDS epidemic as a public health threat by 2030 are being instituted throughout most national HIV control programs [28]. Recent advances in the fast-track approach to HIV and AIDS in Cameroon has been the recommendation of offering to every client presenting to a clinic for any medical consultation to pass the HIV screening test and to allow as many people to know their HIV status [29]. In addition, the government of Cameroon through the Ministry of Public Health has instituted new directions by placing the systematic treatment of HIV under the strategy called test and treat (screening and treatment) [29]. This new strategy requires that any person screened and confirmed positive for HIV is directly placed on antiretroviral treatment. Proper retention in care and a high level of adherence are needed to sustain lower viral load counts and reduce chances of drug resistance that might result from treatment defaulting. More people will be accessing ART services as a result of enhanced HIV testing. There is a high need to devise strategies that would lead to improved retention in care and sustained adherence to treatment.

In this light, the benefits of mobile phone SMS in improving and promoting health outcomes are warranted, particularly in this era of increased uptake and use of mobile phone devices. However, there is a paucity of economic data to support the use of mHealth behavioral interventions in low- and low-middle–income countries [30].

Improving retention in care and promoting adherence to treatments can play a key role in reducing the morbidity and mortality associated with HIV and tuberculosis diseases. The occurrence of drug-resistant strains and the waste of medication in health systems can be adequately managed. Findings generated from this trial may be generalizable to other chronic illnesses requiring lifelong treatments.

A major ethical concern is the harm that might be caused to participants due to the accidental disclosure of their disease status. This possibility shall be properly explained to the participant, even though our text messages shall neither disclose status nor make mention of medication but shall rather act as a reminder of health. Loss of privacy and confidentiality are not foreseeable problems in the study. The intervention shall be an addition to an already existing system in Cameroon where mobile operators deliver messages to their clients for business purposes. The text messages shall be delivered to the participants’ mobile phones by the research team using phones with prepaid airtime.

The content of the SMS was developed following the construct of the health belief model of behavior change. Furthermore, the intervention shall focus on the health belief model. Collected data shall be used to test the efficacy of the SMS reminder as a cue to action. This study is timely, as it is based on this strategy to improve and promote ART and tuberculosis treatment adherence and retention in care in Cameroon. Furthermore, the study will enhance our understanding of the extent that mHealth intervention promotes healthy behaviors and support psychosocial well-being among patients receiving treatment for chronic diseases. The study shall also investigate the effect of tuberculosis coinfection on the health outcomes of HIV clients. Therefore, the study will contribute to an improved understanding of which type of text message frequency can be feasible when, why, and for whom.

## Abbreviations

ART: antiretroviral therapy
CONSORT: Consolidated Standards of Reporting Trials
mHealth: mobile health
PIT: pill identification test
PRD: pharmacy refill data
VAS: visual analog scale
